## Abstract

**Background:**

Adoption of modern contraceptive methods after menstrual regulation (MR) is thought to reduce subsequent unwanted pregnancy and abortion. Long-acting reversible contraceptives (LARCs) are highly effective at reducing unintended pregnancy, but uptake in Bangladesh is low. Providing information on the most effective methods of contraception increases uptake of more effective methods. This protocol describes a randomised controlled trial of an intervention delivered by mobile phone designed to support post-MR contraceptive use in Bangladesh.

**Methods:**

This is a multi-site single blind individual randomised controlled trial. At least 960 women undergoing MR procedures at selected facilities will be recruited after their procedure by female research assistants. Women will be randomised into the control or intervention group with a 1:1 ratio.

All participants will receive usual clinic care, including contraceptive counselling and the telephone number of a non-toll-free call centre which provides counselling on MR and contraception. During the 4 months after their MR procedure, intervention participants will be sent 11 recorded interactive voice messages to their mobile phone about contraception with a focus on their chosen method and LARCs. Each message allows the participant to connect directly to the call centre. The intervention is free to the user. The control group will receive no messages delivered by mobile phone. All participants will be asked to complete an in-person questionnaire at recruitment and follow-up questionnaires by telephone at 2 weeks, 4 months and 12 months after their MR. The primary outcome for the trial will be self-reported LARC use 4 months post-MR. Secondary outcomes include LARC use at 2 weeks and 12 months post-MR, use of any effective modern contraceptive method at 2 weeks, 4 months and 12 months post-MR, and contraceptive discontinuation, contraceptive method switching, pregnancy, subsequent MR and experience of violence during the 12 month study period.

**Discussion:**

Mobile phones offer a low-cost mechanism for providing individualised support to women with contraception outside of the clinic setting. This study will provide information on the effects of such an intervention among MR clients in Bangladesh.

**Trial registration:**

Trial registered with clinicaltrials.gov Registration number: NCT02579785 Date of registration: 16th October 2015.

## Background

Abortion is illegal in Bangladesh except to save the life of a women, however ‘menstrual regulation’ (MR) is allowed as an “interim method to establish a state of non-pregnancy in a woman who is at risk of being pregnant” [1]. MR is legal when provided by a registered service provider as a surgical procedure with manual vacuum aspiration (MVA) up to 12 weeks from the last menstrual period or as a medical procedure (menstrual regulation with medication (MRM)) up to 9 weeks gestation using a combination regimen of mifepristone and misoprostol [2, 3]. Economic, cultural and informational barriers limit access to legal MR services and many women still turn to illegal abortions which are often unsafe, putting them at risk of harm [4–6]. MR and abortion incidence can be estimated using facility and population surveys, service numbers and key informant interviews [6, 7]. In 2014, an estimated 430,000 MR procedures took place at health facilities in Bangladesh [8].

Use of modern contraception has the potential to avert the majority of abortion related morbidity and mortality around the world [9, 10]. In Bangladesh, 12% of currently married women aged 15–49 years have an unmet need for family planning [11], this figure is slightly lower than the average for Southern Asia (14%) [12]. The type of contraceptives a woman uses has implications for unintended pregnancies: the contraceptive pill has a failure rate of 8% in the first year of typical use, whereas the most effective reversible methods of contraception, the intra-uterine device (IUD) and the implant (termed long-acting reversible contraceptives or LARCs), have failure rates of between 0.05% and 0.8% in the first year of use [13]. LARCs also have lower discontinuation rates and higher user satisfaction than short-term methods (such as the pill, condom, and injectable) [11, 13–15]. In Bangladesh, 40% of condom users and 34% of pill users discontinue their method within a year, the latter often due to side effects or health concerns; however, the rate of discontinuation for implant users is just 7% [11]. Despite this, short-term methods dominate in Bangladesh, in 2014 the method mix was as follows: 27.0% of married women of reproductive age used the pill, 12.4% used the injectable, 6.4% condoms, 1.7% the implant and 0.6% the IUD [11]. A further 8.4% of women rely on natural methods such as abstinence and withdrawal and 5.8% use sterilisation [11]. Interventions have demonstrated that removal of barriers to LARC use, such as knowledge gaps and cost, can increase uptake of these methods [14, 16].

Interventions are needed to support continuation and correct use of short-term methods and to address barriers to use of LARCs and permanent methods of contraception among Bangladeshi women at risk for unwanted pregnancy. MR clients are a key population to target as they often want to delay or limit future pregnancies. The WHO recommends provision of post-abortion family planning as an effective way of reducing subsequent unwanted pregnancy and abortion [17]. Most facilities in Bangladesh offer post-MR family planning counselling and services however gaps remain: the full range of contraceptive methods is not always available and counselling is often limited to the day of the procedure as WHO does not currently recommend routine follow-up for MR cases [17, 18].

Globally, some evaluations of mHealth interventions have demonstrated that they can be effective in improving health behaviours and outcomes, but the evidence is limited and outcomes are mixed [20, 21]. Findings suggest that multifaceted approaches may be more effective but further research is required to establish how to optimise interventions [20]. Evidence for the effectiveness of mHealth interventions aimed at improving contraceptive use is limited and shows mixed results [22]. One trial focused on post-abortion contraception and found that interactive voice messages linked to call centre counselling sent to abortion clients in Cambodia were successful in increasing contraceptive use at 4 months but not at 12 months [16].

This trial aims to examine the effects of an intervention delivered by mobile phone designed to support contraceptive use among public and private sector MR clients in three divisions of Bangladesh. The trial hypothesis is that the women who receive a multi-component mHealth intervention will have higher rate of LARC use at 2 weeks, 4 months and 12 months post-MR, compared to women who do not receive the mHealth intervention.

## Methods/design

### Trial design

The intervention will be evaluated using a multi-site, single-blinded RCT. Participants are randomized to the intervention (interactive voice messages that optionally link to telephone counselling in addition to standard care plus the call centre number) or control (standard care plus call centre number) with a 1:1 ratio.

### Study setting

Women will be recruited from Marie Stopes Bangladesh (MSB) facilities and public sector facilities that are supported by Ipas Bangladesh. MSB operates 140 clinics that offer sexual and reproductive health services including family planning, post-abortion care (PAC) and MR across the country. Ipas Bangladesh currently supports 82 government and non-government Reproductive Health Services Training and Education Programme (RHSTEP) facilities, providing training on woman-centred MR, PAC and post-abortion family planning for physicians and mid-level providers working in intervention clinics.

MSB and public-sector clinics supported by Ipas will be eligible to participate if they are in Dhaka, Chittagong or Sylhet Division, have an average monthly case load of at least 20 MR clients and have no other intervention studies underway. Eligible clinics will be stratified into primary, secondary and tertiary levels to ensure representation from all facility types as these facilities serve different populations of women. Primary level clinics are smaller clinics and are in rural and peri-urban areas. Secondary clinics are larger clinics located in urban areas; they provide a wider range of services and act as referral points for the primary level clinics. Tertiary clinics are hospitals located in large cities.

Seventeen sampling units of 19 participants will be selected at random from the list of eligible facilities in each strata using probability proportional to size based on mean monthly client flow in the past 3 months. If recruitment monitoring shows these clinics will not achieve full recruitment within the specified time-frame further clinics will be recruited. This will ensure 323 clients are recruited per strata, to allow between strata comparison, yielding a total sample of 969.

### Eligibility criteria

All women who meet the following inclusion criteria will be eligible for participation: (1) received MR with MVA or MRM from a participating clinic; (2) 18–49 years of age; (3) did not receive general anaesthesia for their MR procedure; (4) have a personal mobile telephone; (5) consent to receiving voice messages about family planning on their phone; (6) don’t intend to become pregnant within the next 6 months and (7) don’t intend to use (or for their partner to use) a permanent method of contraception in the next 6 months.

### Recruitment procedure

Participants will be recruited using the following steps, stages 1–4 are standard in the MR services provided at all MSB clinics and government facilities supported by Ipas. 1. MR is discussed with the client, the type of MR procedure is chosen and family planning is introduced, if a client wants an IUD fitted during the MVA procedure, this is agreed now. 2. The MVA procedure takes place or mifepristone (an oral pregnancy termination medication, also called RU486) is administered. 3. MVA clients can visit a recovery room. 4. Post-MR counselling is provided, including further discussion of family planning. Contraceptive method(s) are provided if desired. MVA clients can start any contraceptive method on the day of MR procedure, MRM clients can start any method apart from an IUD or female sterilization which can be provided after non-pregnancy has been established. 5. If the client is interested, she will be referred to a female research assistant (RA) who will explain the study and enrol her if she wishes. Alternatively, clients can return to the clinic within 2 days of their MR procedure for further information and enrolment. 6. Women who choose to participate will be asked to sign or thumbprint an informed consent form. Consent forms will also be signed by the interviewer and by a witness chosen by the client.

No financial incentives will be received for recruiting participants. Women participating in the study will receive 300 taka (approximately US$3.83 in February 2016) in cash at the time of enrolment as a token of appreciation for their time. They will receive an additional 100 taka for the short interview at 2 weeks post-MR and 200 taka for each of the longer follow-up interviews (at four and 12 months post-MR) using phone credit. To reduce loss to follow up, participants will be asked for any alternative phone numbers that can be used to contact them to conduct follow up interviews if we cannot reach them on their primary number.

To ensure the potential participants fully understands the intervention and to verify that it is not likely to put her at risk of harm, an example message will be played on the either the client’s or RA’s phone during recruitment (prior to randomisation) and the RA will explain how to use the interactive functions. After the message has been heard, the RA will ask the client whether she is happy to receive this type of message on her phone and what would happen if their husband, partner or someone else like her in-laws or other family member heard the message. If any concerns are raised the client will be advised not to participate and if necessary referred for further support.

### Randomisation

The allocation sequence will be generated remotely by a researcher at an independent research institute prior to the start of recruitment in Excel using the formula “=RANDBETWEEN(1, 2)”. The list will be password protected and only the independent researcher and a London based non-researcher (as a back-up) will have access to it. After each enrolment, RAs will send a unique participant ID and the participant’s phone number, family planning method and preferred message time slot to a technical officer based at the Marie Stopes Bangladesh (MSB) head office in Dhaka via a secure app. At the end of each day, the technical officer will email the IDs of new participants to the independent researcher for randomisation. The independent researcher will allocate participants to either the intervention or control group using the pre-generated randomisation list. On receiving the allocations from the independent researcher, the technical officer will initiate the intervention for those participants in the intervention group. This method will ensure allocations are concealed from the RAs recruiting clients and to service providers. Allocations will be concealed from RAs conducting the follow-up interviews during collection of data on the primary outcome and will also be concealed from one data analyst. Allocations are expected to be assigned within 2 days of enrolment. It will not be possible to blind participants to their allocation group. RAs conducting recruitment will not be un-blinded during the trial period.

### Intervention

The intervention was designed in 2015 based on 24 in-depth interviews with MR clients [23], literature reviews on barriers to and predictors of contraceptive use in Bangladesh, global evidence for the effectiveness of interventions delivered by mobile phone and behavioural theory [24]. Draft message content was tested with the target group. Full details of the development process will be reported elsewhere.

Each participant will be sent a series of 11 automated, interactive voice messages sent to their mobile phone over a 4-month period, starting within a week of the MR procedure. Messages will be sent weekly for the first 6 weeks and fortnightly for the following 8 weeks. The recorded messages, which are free to receive, start playing when the phone is answered and are delivered through a secure online platform from ‘I Am Digital’ in Dhaka. If the call is not answered it is re-sent after 30 min and again after another 30 min. At the end of each of the 11 messages, the recipient can press keys one to five to select one of the following options: (1) repeat the message; (2) listen to one or more of seven additional messages, one about each modern method of contraception (condoms, pills, injectable, implant, IUD, male and female sterilization); (3) speak to a call centre counsellor; (4) report that they are fine and don’t need further information today or (5) opt out from receiving further messages. At recruitment, the participant is asked to select one of five time slots for receiving the messages. The content of the 11 messages is tailored to the individual’s chosen method as follows: the method of contraception received at the clinic is used to allocate participants to one of six message groups: no method users, condom users, pill users, injectable users, implant users and IUD users. Seven core messages will be sent to all participants reminding them of the benefits of using contraception, addressing key barriers such as fear of infertility and addressing information gaps, particularly around LARC and permanent methods. The remaining four messages will be specific to the method group for example, pill users will receive the seven core messages plus four messages tailored to supporting pill use. For current contraceptive users, the tailored messages provide information and support for continuation and correct use of their chosen method, they also aim to promote safe-switching among women who are not happy with their method. The tailored messages sent to non-users are designed to encourage uptake of contraception. Women are reminded at recruitment and in the messages to inform the call centre counsellor if they switch contraceptive methods. The messages do not mention MR or refer to the participant’s clinic visit to prevent their MR status being disclosed should someone else answer or overhear the call.

The call centre is operated by three paramedics who have received training on MR, contraceptives and counselling. Women who contact the call centre are referred to MSB clinics or government facilities for services if needed.

Both control and intervention groups will receive post-MR counselling provided at the facility and information about the call centre which can be called at the cost of a standard call to a mobile phone. Women assigned to the control group will not receive any intervention messages.

### Data collection

Data collection tools will be developed in English then translated into and administered in Bangla. Where possible we will use or adapt existing tools including questions from the Bangladesh Demographic Health Survey [25]. On the first day of recruitment, data on the family planning services available at participating facilities will be collected from the facility manager or MR provider using a questionnaire administered by an RA (following informed consent). Study participants will be interviewed by the recruiting RA after enrolment to collect data on demographics (poverty level will be measured using the Progress out of Poverty Index (PPI)), reproductive history and intentions, the current MR and any family planning counselling and methods received, household decision making, experience of violence, type and frequency of mobile phone usage, contact phone number and preferred time of day to receive messages and to be contacted for follow up interviews.

Female RAs based at the MSB head office will administer follow-up questionnaires by telephone. The 2-week interview lasting approximately 5 min will ask about current contraceptive use. Changes in contraceptive method among intervention participant will be made in the online platform administering the messages. The 4-month and 12-month questionnaires will last approximately 15 min and will ask about marital status, fertility intentions, experience of violence, contraceptive use in the preceding months/weeks, any pregnancies or MR procedures, contraceptive discontinuation and reasons for stopping a method. Information on side effects will be collected where it led to discontinuation of a method. The 4 and 12 month follow up survey questions will be the same except that the time frame for some questions will differ and the 4-month survey will include measurement of hypothesised intermediate outcomes and questions to assess use of and satisfaction with the intervention and any related privacy concerns. Questions on the outcome will be asked at the start of the interview, prior to questions about the intervention.

All contraceptive use and non-use since baseline will be recorded using a modified version of the Demographic and Health Survey contraceptive calendar [25]. Participants will be asked at recruitment whether they consent to the study team accessing their clinic records to verify reports of MR procedures and LARC insertions or removals.

To ensure high participation in follow-up interviews we will collect a range of contact data for each participant and will ask participants to inform us if their contact details change. The reimbursements at each follow-up interview are also expected to increase participant retention.

#### Use of the intervention

Data on use of the intervention such as whether recorded voice messages are listened to and whether clients interact with the messages will be generated by the mHealth platform. Calls to the call centre will be monitored; call centre operators will complete a standard form for every caller to collect basic information on who the caller is (participant themselves, husband, friend etc.) and the reason or reasons for the call. A small number of calls will be audio recorded.

### Outcome measures

Primary and secondary outcomes and the methods of data collection are summarised in Table 1.

**Table 1 Tab1:** Outcome variables and analysis methods

Outcome	Questionnaire	Outcome measure	Method of analysis
Primary			
LARC use	Baseline, 2-week, 4-month & 12-month	Self-reported (binary)	Logistic regression
Secondary			
Use of any modern contraceptive	Baseline, 2-week, 4-month & 12-month	Self-reported (binary)	Logistic regression
Pregnancy	4-month & 12-month	Self-reported (binary)	Logistic regression
MR	4-month & 12-month	Self-reported (binary)	Logistic regression
Discontinuation/ Method switching	2 week, 4-month & 12-month	Self-reported (#of times, continuous)	Log Rank test Kaplan Meier Curves
Experience of violence	4-month and 12 month	Self-reported (binary)	Logistic regression

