#### Secondary outcomes

Secondary outcome measures include current use of any effective modern contraceptive method at 2 weeks, 4 and 12 months post MR. We define modern contraceptive methods according to the WHO as those associated with <10% 12 month pregnancy rates [13]. These will be measured as having had or having a partner who has had sterilization, currently have a sub-dermal implant or an IUD inserted, have received the injection in the last 3 months, currently using the contraceptive pill and reporting that they always or usually take the pill on time. Further secondary outcomes are self-reported pregnancy at the time of the four and 12 month interviews, having had an MR since enrolment into the study and having experienced violence since enrolment. Data from the contraceptive calendar will be used to estimate a point prevalence of contraceptive use at any given time and contraceptive discontinuation rates.

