### Sample size

Sample size calculations were based on the primary outcome: LARC use 4 months after the MR procedure. Based on approximately 28,000 MR procedures conducted between November 2011 and June 2013 in government facilities supported by Ipas and approximately 16,500 in MSB clinics between October and December 2013, 7.0% of women are expected to select an IUD as their post-MR contraceptive method and 2.4% an implant, resulting in an expected 9.4% LARC uptake at baseline. A similar mHealth trial in Cambodia saw LARC use at 4 months increase from 9% to 29% with receipt of the intervention. Given the low cost of sending automated phone messages, a smaller increase may be programmatically important. To detect an absolute increase in LARC use of 7%, from 9.4% in the control group to 16.4% in the intervention group (a relative risk of 1.74), at four-month follow-up with a 0.05 significance level and 80% power, and assuming equal numbers of women in intervention and control groups the study needs a minimum of 714 participants. We increased this to a minimum of 960 to allow for 25% loss to follow-up (Fig. 1).

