### Training and monitoring

Research Assistants enrolling participants into the study and collecting baseline data will attend a 5-day training in Dhaka led by one international and one local investigator. Five supervisors will be trained to conduct supervision visits to ensure study protocols are being followed. Supervisors will be given a checklist to complete at each visit. Regular monitoring visits will be made by the study manager during enrolment and data collection to ensure study protocols are being followed and to identify any problems with recruitment or data collection. If necessary, further guidance or training will be provided to data collectors. Research Assistants conducting follow-up surveys will receive up to 5 days training (dependent on whether they have previous involvement in the study). Follow up data collection will be monitored by the study manager during daily de-briefs.

No data monitoring committee will be established for this trial as the likely risks to participants of receiving an mHealth intervention are known to be minimal. All adverse events reported to the study team during follow up surveys or via calls to the study or call centre numbers will be reported by the study manager to the principal investigator within 1 week of their occurrence. The response will be agreed with the other study investigators and where appropriate reported to the ethical committees.

The protocol and intervention were reviewed by an in-country advisory committee who will meet intermittently to review progress and give input. The committee includes the Director of Primary Health Care and Director of Continued Medical Education at the Directorate General of Health Services; the Director of Maternal and Child Health services and the Director of Information, Education and Motivation at the Directorate General of Family Planning; Executive Director, Reproductive Health Services, Training and Education Programme (a non-governmental organisation working in Government of Bangladesh Hospitals); Director, Bangladesh Association for Prevention of Septic Abortion; President, Obstetric and Gynaecological Society of Bangladesh; Country Director, Population Council; Chief Executive Officer, Bangladesh Centre for Communication Programme; Senior Director, Marie Stopes Bangladesh; Country Director, Ipas Bangladesh.

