### Data analysis

We will adhere to the CONSORT guidelines for reporting RCT conduct and outcomes. Intention-to-treat principles will be used for primary outcome analysis, meaning all participants will be analysed according to the arm to which they were randomised. We will investigate the patterns of missing data, and will report any treatment group imbalances between those who do and do not complete the study.

The primary analysis, using multiple imputation to handle missing data (as detailed below), will be a logistic regression of 4-month LARC use on treatment and baseline use. For the primary analysis, we assume data are missing at random, given treatment group, 2-week and baseline LARC use, baseline socio-economic status (SES) and age. Under this assumption, multiple imputation of missing 4-month data will be performed separately for the two intervention groups, by full conditional specification, using the following variables: baseline, 2-week and 4-month LARC use, together with auxiliary variables, baseline SES and age. The multiple imputation procedure will also impute any missing baseline data (under the same assumption). One hundred imputed datasets will be created, and the imputation process will be checked for convergence and perfect prediction.

The primary analysis will be validated by an analysis under the slightly stronger assumption that data are missing at random, given treatment group, baseline LARC use, baseline SES and age. This can be achieved with a logistic regression of 4 month LARC use on baseline LARC use, intervention group, baseline SES and age. Robustness of inference from the primary analysis to the missing at random assumption will be explored using the “δ -method” for information-anchored sensitivity analysis [26].

Keeping the information in the data constant, this method allows us to explore the robustness of our conclusions about treatment to the missing at random assumption (MAR). In this study, MAR assumes that — among patients in the same treatment group, with similar baseline data and similar early follow-up — the odds of LARC use at the end is the same whether or not their data are missing. This assumption is untestable, so the “δ -method” explores how the conclusions vary as — still among patients in the same treatment group, with similar baseline data and similar early follow-up — the odds of LARC use at the end differs by δ between patients with observed and missing data.

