Contraceptive discontinuation rates will be estimated over the one-year project period using Kaplan-Meier curves, overall and by family planning method. The log-rank test will be used to test for differences in discontinuation rates between methods. Table 1 summarizes the method of analysis for the primary and secondary outcomes. We will use Stata to conduct data analysis [24]. Data on use of the messages and details of calls made to the call centre will be analysed descriptively. Sub group analysis will be conducted to explore whether the intervention effect varies according to age, education, SES, type of MR procedure (medical vs surgical), experience of violence in the last year (yes/no), and on who makes decisions about whether the participant uses contraception (self/self and one or more other person/other person).

Transcripts from the calls to the call centre will be analysed qualitatively to examine the type of information and/or support the counsellors provide to enable a more detailed description of the intervention.

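### Baseline violence is collected, but no adjustment for it is stated in the violence analysis; adding it would usually gain a few points of power

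*Protocol article*

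**What the plan says.** Everything here is in the protocol article.

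- **Outcome.** Under Secondary outcomes, violence is counted from enrolment onwards: "having had an MR since enrolment into the study and having experienced violence since enrolment".
- **Method.** The Table 1 row "Experience of violence" gives a binary self-reported measure, the 4- and 12-month questionnaires, and logistic regression. Data analysis adds: "Table 1 summarizes the method of analysis for the primary and secondary outcomes".
- **Baseline measurement.** Under Data collection, the enrolment interview covers "household decision making, experience of violence, type and frequency of mobile phone usage".
- **Stated use of the baseline value.** In Data analysis it appears once, in the list of subgroup factors, as "experience of violence in the last year (yes/no").
- **Primary outcome, for comparison.** The primary analysis "will be a logistic regression of 4-month LARC use on treatment and baseline use".
- **Questionnaire column of Table 1.** Baseline is listed for LARC use and for use of any modern contraceptive. It is not listed for violence.

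**The concern.** The trial adjusts its primary outcome for the same variable at baseline. It measures violence at baseline too and has a yes/no definition ready, but states no corresponding adjustment for the violence outcome.

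The comparison matters because the investigators see a possible route to harm. Under Recruitment procedure, each woman is asked before randomisation what would follow if her husband, in-laws or others heard a message, and she is advised against joining if concerns arise. Violence is the Table 1 outcome closest to that risk.

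Allocation is a simple random draw in Excel with no stratification, so nothing in the design balances baseline violence between arms. If the baseline value is left out, some power is given up and a chance imbalance stays in the point estimate.

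**Working it through.** **1. The plan's own figure.** The sample size is set for LARC use, 9.4% against 16.4%, "at four-month follow-up with a 0.05 significance level and 80% power". With unpooled variances and a two-sided test:

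n per arm = (1.960 + 0.842)² × (0.094 × 0.906 + 0.164 × 0.836) / 0.07² = 7.849 × 0.22227 / 0.0049 = 356.03, rounded up to 357, so 714 in total.

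This matches the protocol. The minimum of 960 less 25% loss leaves 720, or 360 per arm. No rate or power is stated for violence.

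**2. Assumptions.** None of these is in the document: baseline prevalence 10% or 30%; control-arm violence at follow-up 5%, 10% or 20%; baseline-to-follow-up odds ratio 3, 5 or 10; conditional treatment odds ratio 1.5 or 2.0. That makes 36 scenarios.

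**3. Formulas (large-sample).** Model: logit P(violence) = a + t·arm + b·baseline.

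- Unadjusted: effect = log of the marginal odds ratio; SE = √[1/(360·r0(1−r0)) + 1/(360·r1(1−r1))], where r0 and r1 are the arm rates.
- Adjusted: effect = t; SE = 1/√[Σ w0·w1/(w0+w1)], summed over the two baseline groups, where w = n·p(1−p) in each arm.
- Power = Φ(effect/SE − 1.96).

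**4. Worked case.** Prevalence 30%, control rate 10%, baseline odds ratio 5, treatment odds ratio 2.0.

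| | n per arm | Control risk | Intervention risk | w0 | w1 |
|---|---|---|---|---|---|
| No baseline violence | 252 | 0.0514 | 0.0978 | 12.29 | 22.23 |
| Baseline violence | 108 | 0.2133 | 0.3516 | 18.12 | 24.62 |

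- Unadjusted: r1 = 0.7 × 0.0978 + 0.3 × 0.3516 = 0.174; marginal odds ratio 1.90; SE = √(0.03086 + 0.01933) = 0.224; z = 0.6395/0.224 = 2.85; power 81.4%.
- Adjusted: information = 7.91 + 10.44 = 18.35; SE = 0.233; z = 0.6931/0.2334 = 2.97; power 84.4%.
- Gain: 3 points of power; (2.970/2.854)² = 1.08, equivalent to 8% more women.

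The standard error goes up, from 0.224 to 0.233. Power rises because the conditional odds ratio (2.00) lies further from 1 than the marginal one (1.90).

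**5. All 36 scenarios at 720 women.**

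| | Scenario | Power without | Power with | Effective sample size |
|---|---|---|---|---|
| Among the smallest gains | prevalence 10%, control 20%, baseline OR 3, treatment OR 2.0 | 97.3% | 97.6% | +3% |
| Largest gain | prevalence 30%, control 20%, baseline OR 10, treatment OR 1.5 | 42.8% | 51.7% | +27% |

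The gain runs from 0.3 to 8.9 points and is below 5 points in 31 of the 36. Effective sample size rises by 1% to 27%, and by 2% to 15% in 29 of the 36. The adjusted standard error is larger in every scenario.

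**6. Chance imbalance.** With 360 per arm, the 95% limit for the difference in baseline prevalence is 1.96 × √(2π(1−π)/360): 4.4 points at 10% prevalence and 6.7 points at 30%. In the worked case with no treatment effect, baseline prevalences of 33.3% and 26.7% give arm rates of 0.0514 + 0.333 × 0.1619 = 0.105 and 0.0514 + 0.267 × 0.1619 = 0.095. The unadjusted odds ratio is then about 1.13, in whichever direction the imbalance falls.

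**The case against.** **The text does not say the model is unadjusted.** Table 1 gives the primary outcome the same bare label, and Data analysis shows that model is adjusted for baseline. So the label names a model family and settles nothing about covariates, and covariates for secondary outcomes are often left to an analysis plan, which is not shown here. This stands as far as it goes: a reader might infer that the protocol specifies a plain unadjusted model, and it does not. But Table 1 lists the baseline questionnaire for the two contraceptive-use outcomes and leaves it out for violence, although violence is asked at baseline. Not using the baseline value is therefore the more natural reading.

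**Unadjusted logistic regression is valid here.** This stands. Chance imbalance is already reflected in the test's error rate and is not a bias.

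**The gain is assumed and adjustment is not free.** This stands too. Every violence rate above is an assumption, and so is the strength of the link between past and later violence. Screening before randomisation could lower violence rates below those assumed.

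**Violence is not the only safeguard.** This stands. The protocol also has risk screening, messages that do not mention MR, an opt-out at each message, questions on privacy concerns at 4 months, and adverse-event reporting: "All adverse events reported to the study team during follow up surveys or via calls to the study or call centre numbers will be reported" to the principal investigator.

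**Conclusion.** The point holds as an optional, low-priority improvement. The protocol collects a baseline value, defines it as yes/no, and states no use of it in the model for the same outcome at follow-up, although the primary analysis makes that use of baseline LARC use. Adding it would usually gain a few points of power at 720 evaluable women (about 0.3 to 9 over the assumed range) and would take a chance imbalance in baseline violence out of the estimate.

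Three stronger readings are tempting and not supported:

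- **That violence is the trial's only pre-specified harm outcome, or its main safety check in the absence of a data monitoring committee.** The document never labels it so and describes other safeguards. A covariate in a follow-up regression does not replace monitoring in any case.
- **That adjustment narrows the interval for the log odds ratio.** Its standard error rises; power improves because the quantity estimated is now the conditional odds ratio, which lies further from 1.
- **That the change costs nothing.** The costs are small, but they exist.

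**What to change.** In Data analysis, state that the 4- and 12-month violence models include baseline past-year violence (yes/no) as a covariate with treatment, as the primary model does for baseline LARC use. Add 'Baseline' to the questionnaire column of the violence row in Table 1. Settle this before any unblinded analysis, so that the choice between adjusted and unadjusted results is not made after seeing them.

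No new data are needed. Report the odds ratio as conditional on baseline violence, accept the slightly larger log-scale standard error, and say how missing baseline answers are handled (the primary analysis already plans to impute missing baseline data). If violence proves rare, check for sparse cells before relying on the adjusted model.
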